### Data monitoring

3.15

This pilot RCT has been designed for conciseness and minimizing risk. Therefore, no formal data monitoring committee has been organized. In addition, no interim analysis of the intervention's impact has been planned at this stage.

### Harm

3.16

Previous studies have reported no adverse events with the use of the SPSRS application. However, adverse events will be systematically monitored based on the methods used in previous studies,^[54]^ while prompt responses will be provided for incidences and signs of adverse events. Participants are encouraged to identify signs of mental or physical health deterioration upon study enrollment, regardless of whether they participate the intervention. The appearance of such symptoms will be considered an adverse event.

Participants will be taught 2 methods of identifying adverse events during and after the study. First, participants will be encouraged to talk to their researchers upon noticing signs of mental or physical health deterioration. Second, all study participants will be requested to inform the research team whether and why they plan to discontinue with the study. Upon the occurrence of an adverse event, the participant will be contacted and appropriate action will be taken. The investigator will also evaluate and document the participant's relationship with the study in addition to the content, duration, severity, and outcome of the adverse event.

Details regarding adverse events will be immediately reported to the Kibi International University Ethics Review Board who will then determine the direction of the study.

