#### Control group

3.2.2

The control group will receive no intervention and no instruction to watch videos using the SPSRS application or other video playback applications during the 5-week intervention period.

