### Strategies for monitoring and improving intervention protocol adherence

3.3

The amount of time participants spend on viewing videos during the intervention will be recorded in the history function of the SPSRS application and will be used for treatment adherence monitoring once a week. Participants who achieve the required video viewing duration per week (i.e., ≥70 minutes) will receive a text message to encourage continued video viewing. However, those who did not meet the required video viewing duration per week will receive a text message informing them regarding the same. In addition, a text message will be sent requesting the participant to make up for the missed viewing time on the subsequent week. Moreover, daily text messages will be sent to encourage the use of the SPSRS application and increase intervention adherence rates.

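### Adverse-event monitoring is called systematic, but both methods described wait for the participant to report and scheduled contact reaches only the app arm, so event counts may not be comparable between arms

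*Protocol article*

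**What the plan says.** Section 3.16 (Harm) states that "adverse events will be systematically monitored based on the methods used in previous studies". It asks both arms to watch for deterioration: "Participants are encouraged to identify signs of mental or physical health deterioration upon study enrollment, regardless of whether they participate the intervention". Any such deterioration is an adverse event.

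It then names two methods that participants will be taught:
- Method 1 is a self-report: "First, participants will be encouraged to talk to their researchers upon noticing signs of mental or physical health deterioration".
- Method 2 is a request to everyone in the trial, in either arm, to let the team know if they intend to stop, and for what reason.

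The team's own contact comes afterwards: "Upon the occurrence of an adverse event, the participant will be contacted and appropriate action will be taken".

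On contact during the 5 weeks, section 3.3 says the viewing time logged by the app "will be used for treatment adherence monitoring once a week", with a text each week on whether the target was met, and that "daily text messages will be sent to encourage the use of the SPSRS application and increase intervention adherence rates". For the other arm, section 3.2.2 says: "The control group will receive no intervention and no instruction to watch videos". Section 3.10 states that participants and therapists cannot be blinded.

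**The concern.** A participant-initiated system records an event only if the participant notices it, thinks it relevant and takes the trouble to report it. A system normally called systematic puts the same question to everyone at set times. The article uses that word and then describes the passive kind.

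This matters more where the arms differ in how present the study is to participants. App users hear from the study every day. For controls no contact is described between allocation and week 5. The readiness to report could therefore depend on arm, and unblinded participants may also attribute symptoms differently.

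At stake is what the pilot can say about harm. The Introduction lists harm among the issues to be addressed before a full-scale trial. There is no data monitoring committee (3.15) and no audit (3.17). Under 3.16 the ethics board decides the direction of the study from the adverse events reported to it.

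**Working it through.** The documents give no adverse-event rate, reporting probability or harm comparison, so there is no stated figure to reproduce. The check compares the relevant sections and then illustrates the mechanism with assumed values.

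**How events are found (3.16)**
- Method 1: the participant approaches the researchers. Open to both arms, participant-initiated.
- Method 2: the participant announces a planned discontinuation and the reason. Addressed to all participants, participant-initiated.
- Team contact: follows a known event.
- Scheduled question on harm: none described.

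**Scheduled contact before week 5**
- Experimental arm: daily texts and a weekly text on viewing time (3.3), after a manual and training at the start (3.11).
- Control arm: none described (3.2.2).
- Email address in 3.12: for concerns about using the app.
- Contact open to both arms: researchers can be reached during the trial and for 1 month afterwards (3.21), again on the participant's initiative.

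**What is measured alike in both arms**
- Change in CES-D, K6 and GAD-7 after 5 weeks (3.5), requested even after discontinuation (3.12).
- Analysed as group means in a mixed model (3.14). No statement says that an individual's worsening is counted as harm.

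**Illustration (assumed rates; 16 per arm from 3.7)**

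Let p be the same true event risk in both arms, and let s_E and s_C be the probabilities that an event is reported in the experimental and control arms.
- Expected reported events = 16 × p × s
- Apparent risk ratio = (p × s_E)/(p × s_C) = s_E/s_C
- Chance that no event is seen in an arm = (1 − p × s)^16

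With s_E = 0.9:

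| s_C | Apparent risk ratio | Expected reports at p = 0.20, experimental vs control | No control event seen, p = 0.20 | No control event seen, p = 0.10 |
|---|---|---|---|---|
| 0.9 | 1.0 | 2.88 vs 2.88 | 4% | 22% |
| 0.7 | 1.29 | 2.88 vs 2.24 | 9% | 31% |
| 0.5 | 1.8 | 2.88 vs 1.60 | 19% | 44% |
| 0.3 | 3.0 | 2.88 vs 0.96 | 37% | 61% |

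Example for the third row: 16 × 0.20 × 0.5 = 1.60, and (1 − 0.10)^16 = 0.185.

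Equal reporting gives no distortion. If controls reported more readily (0.5 against 0.9), the ratio would be 0.5/0.9 = 0.56, in the opposite direction. The documents do not say which row applies.

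Separately, even with complete capture, 0 events in 16 leaves a two-sided 95% upper limit of 1 − 0.025^(1/16) = 20.6%. That follows from the sample size and says nothing about unequal reporting. It does show how little information there is, and why losing one or two events matters.

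**The case against.** A reader might go further and infer three things that the documents do not support.

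- **That a planned harm comparison is biased.** Section 3.14 plans group comparisons only for the primary and secondary outcomes, and 3.16 uses adverse events for documentation and reporting to the ethics board. Both reporting methods are open to both arms. The texts are outbound reminders about viewing and are not said to ask about health. Controls can leave the study too, so the second method is not empty for them. Unequal reporting is therefore possible but not established.
- **That deterioration in controls is likely to be missed altogether.** CES-D, K6 and GAD-7 are measured in both arms, so depressive, distress or anxiety symptoms that are still worse at week 5 would show in the scores. What stays exposed is transient or physical deterioration, and recognition of an event before week 5.
- **That volunteered reports are certainly the only source.** The cited monitoring methods and the assessment schedule (Table 1) are not visible, and a journal article may leave forms and intervals to the full protocol.

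The last point carries weight, but not enough to dispose of the matter. The article does more than stay silent on detail: it enumerates its methods, and both are passive. The week-5 scales likewise answer only part of the concern, because nothing says a worsened score is reviewed or counted as harm.

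**Conclusion.** The point holds in limited form. As described, ascertainment is passive despite the claim that it is systematic, and scheduled contact during the 5 weeks reaches one arm only. In an unblinded trial this means that adverse-event counts may not be comparable between arms, and that transient, physical or early events may go unrecorded, particularly in controls.

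Neither the size nor the direction of any difference can be derived from the documents. The ratios of 1.0 to 3.0 rest wholly on assumed reporting probabilities and on equal true risk. The conclusion also assumes that the full protocol does not already contain a solicited query put to both arms; if it does, the article's description should be corrected to say so. Sample size and primary analysis are unaffected. This is a modest point, worth acting on because the remedy is cheap.

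**What to change.** Amend section 3.16 as follows.

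1. Add the same short adverse-event questions to the week-5 Internet questionnaire in both arms: any mental or physical deterioration since the start, its onset, its severity, and whether care was sought.
2. Keep the two existing methods, and report solicited and spontaneous events separately by arm, with the number who answered the questions as denominator for the solicited events.
3. Tabulate by arm the number of participants whose CES-D, K6 or GAD-7 score was higher at week 5 than at baseline. On all three scales a higher score is worse. These counts are descriptive and need no test.

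The cost is a few extra items in a questionnaire already used for both arms and one further table. Recorded event counts will rise, and the report should explain that this reflects asking. A week-5 question relies on recall over 5 weeks: it makes recording equal between arms but does not bring earlier events to the team's notice any sooner.

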### Auditing

3.17

No audit has been planned at this time.

### Research ethics approval, protocol amendments, and consent

3.18

This trial has been approved by the Ethics Review Committee of Kibi International University (approval number: 19–33). Prior to participation, the principal investigator or collaborators will inform the participants regarding the details of this trial using trial information materials. Changes to the study protocol will require approval from the Kibi International University Ethics Review Board. Before obtaining informed consent, the researchers will briefly explain the potential risks and benefits of study participation. Documentation of the participants’ satisfaction with the risks and benefits is essential. The researchers will also inform participants that participation is optional and can be discontinued at any time. Informed consent, which will be presented through an Internet questionnaire and obtained by pressing the consent button when the participant agrees to participate in the trial, will be obtained before any intervention is provided.

### Confidentiality

3.19

All information related to the study will be stored securely at Kibi International University. Paper documents will be stored separately for each participant. All survey materials will be identified using participant numbers and stored inside a lockable shelf to maintain participant confidentiality. Information that could potentially identify a participant, such as informed consent, will be kept separate from the survey material identified using participant numbers. The electronic database will be stored on a password-protected Universal Serial Bus and stored together with the paper survey materials. Information regarding a participant's identity will not be entered into the electronic database. Data input and statistical analysis will be conducted on a computer not connected to the Internet at Kibi International University.

### Access to data

3.20

Prior to the publication of major results, only data managers and principal investigators will have access to the complete dataset. Data managers and principal investigators will address problems related to the data and finalize a dataset for statistical analysis. After publication, only the principal investigator and individuals approved by the principal investigator will have access to the dataset.

### Ancillary and post-trial care

3.21

Participants will be able to contact the researchers during the trial period or until 1 month after the end of participation. This trial cannot guarantee the absence of unexpected serious adverse events during and after the participation period. Participants who develop serious adverse events will be responded to promptly and appropriately even after study completion.

### Dissemination policy

3.22

Regardless of the outcome, the trial results will be published in a peer-reviewed journal. Furthermore, participating in and presentations at relevant national and international academic conventions can further promote dissemination.

## Discussion

4

StD has been considered an important risk factor for the development of MDD.^[5,13,14]^ Moreover, despite being a precursor to MDD,^[7]^ StD has been associated with poor quality of life,^[1,7,8]^ poor health,^[9]^ impaired daily activities,^[2,10]^ economic costs,^[11]^ mortality,^[12]^ etc. Therefore, interventions aimed at addressing StD are important to prevent the onset of MDD. Incorporating the SPSRS application into interventions is a very innovative method that places less burden on individuals with StD and may improve depressive symptoms. In addition, given the potential for the SPSRS application to influence numerous individuals with StD, it may play an important role in addressing depressive symptoms that may have a significant negative impact on their health. However, RCTs using the SPSRS application for individuals with StD have been lacking. Therefore, a pilot RCT investigating the feasibility of a large-scale trial to determine the effectiveness of the SPSRS application had been planned. The results of this pilot RCT will undoubtedly ensure the successful implementation of a full-scale RCT. In addition, this pilot trial will provide new information through which a higher-quality full-scale RCT can be planned. A particularly important additional information obtained from results of this pilot RCT is that related to the official sample size calculation. Thus, this pilot RCT can provide evidence that reinforces the standard practice of SPSRS application interventions to improve depressive symptoms among individuals with StD.

This study, however, is not without limitations. First, this pilot study will utilize simple randomization. As a result, other demographic factors, such as age, can lead to sample heterogeneity. Future studies will need to consider stratification of various demographic factors. Second, given the restrictions on the use of the SPSRS application, participants must own an iPhone, thereby excluding those using smartphones running on other operating systems (such as Android). Therefore, our research results may not be generalized to all individuals with StD people. However, we plan to make the SPSRS application compatible with other smartphones (such as Android) for future research, which would considerably increase the number of potential participants. Third, a formal sample size calculation could not be performed given that lack of data on the use of the SPSRS application. This lack of sample size calculation may decrease the power of this pilot RCT. However, retrospective sample size calculation will be performed after this trial. Finally, given the nature of this study, participant and therapist blinding will be difficult. Therefore, some therapist and participant biases may be present. However, we will endeavor to mitigate potential biases resulting from the lack of blinding. For example, research hypotheses will be concealed and standardized intervention guidance and textual feedback will be provided to maintain data quality. Considering the aforementioned limitations, care should be taken in the interpretation of this pilot study's results.

## Conclusion

5

This pilot RCT will have been the first to explore the utility of SPSRS application interventions, which display positive words in videos, for individuals with StD. The results of this pilot RCT are expected to help in the design and implementation of a full-scale RCT investigating the effects of the SPSRS application among individuals with StD.
